#### The control group

Routine intervention: including pressure cold compress, shock wave, microwave and other physical therapies; Soft tissue stretching and relaxation, passive and active joint activity of the ankle, and strength training of muscles around the ankle.

#### The experimental group

TCAWM intervention:

① Physical therapy: infrared dose of 300w, distance of 20cm, irradiate the sick ankle; The shockwave, energy flow density is 0.15mJ/cm^2^, with a pulse count of 2000.

② Exercise training:

a. Muscle strength training: Use elastic bands for ankle dorsiflexion, plantar flexion, inversion, and eversion resistance training, maintain for 10 seconds, perform 20 times in all directions, 2 groups per day;

b. Joint range of motion training: Participants engage in active ankle dorsiflexion, plantar flexion, inversion, and eversion, maintaining a maximum range of motion for 10 seconds, and performing 20 movements in each direction; and perform clockwise and counterclockwise rotation movements of the ankle joint, with gentle, slow, and uniform speed, each rotating 20 times. Two groups per day;

c. Balance training board training: Stand on the balance board, maintain balance with both feet without additional support for 30 seconds, train 20 times, and then maintain balance with one foot without additional support for 20 seconds, alternating between the two feet, each training 20 times, with 2 groups per day;

d. Stable reinforcement training: Conduct in place takeoff training, turn back runs (distance of 100m), each group of takeoff training 50 times, turn back runs 10 times (once in a row). Two groups per day.

③ Acupuncture: local acupoints are the main acupoints, and the acupoints selected are GB40, GB41, BL62, SP5, KI6 and KI5. Warm acupuncture and moxibustion and electroacupuncture can be used.

④ Massage: Select acupoints around the ankle joint, such as GB34, GB40, GB39, KI6, and BL62. The techniques used include pressing, kneading, one finger Zen pushing, stretching, shaking, rubbing, etc. The patient is placed in a supine position, with the physician standing on the affected side and using the thumb massage method to apply pressure to the ankle. First, from the affected area to the surrounding area, and then from the outer ankle through the outer side of the calf to GB34 acupoint, massage three times, with a focus on GB34, GB40, GB39, KI6, BL62 and other acupoints, with a degree of soreness and swelling. Finally, pull and extend the ankle joint several times and perform small internal and external rotations; Then perform ankle joint rocking several times; Wipe the back of the foot using the small thenar wiping method, and extend from the ankle to the calf.

### Outcomes measures

#### Primary outcomes

① Visual Analog Scale (VAS) [38,39]. VAS is used to evaluate the degree of pain. Draw a 10cm horizontal line on the paper with a starting point of 0 and a ending point of 10, marking 0 as painless and 10 as unbearable pain. Mark the corresponding scale every 1cm in the middle of the line. Ask the subjects to mark any position on the horizontal line based on their pain perception, as the degree of VAS pain in the subjects.

② Short form McGill Pain Questionnaire (SF-MPQ) [38,39]. SF-MPQ is used to evaluate pain sensation, with a total of 47 items. The first 11 items evaluate the degree of pain sensation (PRIA), and the 12–15 items evaluate the emotional state of pain (PRIB). The pain level of each item is described as painless (0 points), mild (1 point), moderate (2 points), and severe (3 points). In addition, both pain status and visual analogue scores are now included in the evaluation of overall pain status.

#### Secondary indicators

① Foot and Ankle Ability Assessment Scale (FAAM) [39,40]. FAAM is a method for assessing the degree of daily living ability limitation and ankle mobility disorders, consisting of 21 scores from daily living activities and 8 scores from the Independent Movement Disorder Scale.

② AOFAS Ankle Posterior Foot Scale [41]. Using the American Orthopedic Foot and Ankle Association (AOFAS) Ankle Posterior Foot Scale as a reliable and effective tool for detecting ankle ligament injuries. This standard consists of two main parts, mainly including pain, function and autonomous activity, support, flexion/extension, inward/outward rotation, ankle and foot stability, etc., with a maximum score of 100 points. The two major scores are each 50 points, with a maximum score of 100 points, excellent (90–100 points), good (75–89 points), average (50–74 points), and poor (<50 points). The larger the score, the better the ankle joint function and symptoms.

③ Torque [42]: Peak torque (PT); Peak torque to body weight ratio (PT/BW); Average power (AP); The ratio of bending to elongation peak torque (F/E); The ratio of homonymous contralateral muscles. The testing instrument uses the BIODEX multi joint constant velocity force testing and training system from the United States, and the raw data obtained from the test is automatically generated by the computer. The subject is in a supine position on the seat, and according to their height, body shape, etc., the equipment is adjusted and fixed strictly in accordance with the equipment safety manual. During testing, adjust the seat height and power head scale according to the parameters provided by the software, align the foot movement plane with the foot pedal movement plane, keep the outer ankle in a straight line with the power head rotation center, use nylon ropes to fix the subject’s thighs and feet to the accessories, and perform gravity compensation before testing. Firstly, under the condition of an angular velocity of 60°/s, the subjects were subjected to three maximum contraction exercises of ankle dorsiflexion and plantarflexion. After familiarizing themselves, the subjects rested for 30 minutes to sequentially perform isokinetic muscle strength tests on the healthy and affected ankle joints. Under the conditions of an angular velocity of 30°/s, 60°/s, and 120°/s, active centripetal movements of ankle dorsiflexion and plantarflexion, ankle inversion, and eversion were performed, with 10 consecutive maximum contractions completed each time.

④Gait [43,44]: Step length; Step speed; Step frequency; Supporting phase; Plantar pressure; Ankle flexion and inversion angle [39]. Apply Maiwo Odonate 3D motion capture and gait analysis equipment to test the patient’s walking ability and plantar pressure. The collection end selects gait collection combined with plantar pressure detection mode. Based on the work framework and patch model recommended by the International Society of Biomechanics. The subjects are required to wear tight fitting clothing. Infrared reflector positioning (23 in total). The entire process is carried out by the same senior rehabilitation therapist. Before collection, indicate the patient’s walking area, which is 1.6 to 4.5 meters away from the camera arm. Place the camera arm horizontally and ensure that it is parallel to the ground. Firstly, instruct the patient to stand still at a position of about 2 meters and click on "Static Collection"; Then instruct the patient to stand at a position of about 4.5 meters, click the "Dynamic Collection" button, and instruct the patient to start walking normally on the trail after waving their arms in place.

### Participant safety

When patients participate in this study, they will be required to know the scheme of the whole study and sign the informed consent. To prevent and better treat any injury that may be caused by this study, the researcher will detect any potential adverse events (AEs) and truthfully record on the CRF form. In this study, AEs are mainly including dizziness, shortness of breath, palpitations. If an adverse event occurs, it will be dealt with according to the emergency plan. Researchers will initially determine the severity of AEs. Minor AEs will be treated by the attending physician. Serious AEs will be reported by the researcher to the ethics committee. The correlation between the event and intervention and severity will be evaluated.

### Quality control

The head of the research center will be responsible for the design, coordination and quality control in whole study. All researchers will receive uniform training before the period of data collection. Throughout the research period, a data monitoring of committee independent of researchers and sponsors will extract 10% of case reports from and check the data every three months. The committee will check logic problems, determination of test values, abnormal safety indicators after treatment, vacancy values, compliance, standardization, integrity, consistency, etc. The committee will consist of clinicians, statistician, microbiologist, psychologist, and ethicist.

### Follow up

There will be a follow-up plan to evaluate the long-term efficacy and safety of TCAWM and routine treatment when the protocol ends, the research will follow up the patients after 3 months of the treatment. Participants will not receive any intervene during follow-up. At the end of follow-up, the investigator will make a contract with patients by telephone, E-mail and etc. They will be asked to come to reception room and have a test about VAS、SF-MPQ、FAAM、AOFAS、Torque and gait.

### Sample size

Using data from a previous study [45]. Comparison of sample size estimation formula for two sample means based on bibliometric data, with reference to relevant literature [a] for experimental group VAS (Visual Analog Scale) means μ_2_ = 0.04 after two weeks interventions, while control group VAS (Visual Analog Scale) means μ_1_ = 0.25, the standard deviation σ = 0.45. According to the formula, α = 0.05, β = 0.2, the sample size of each group is calculated to be n = 72, consider a 20% dropout rate, and the final sample size is 87 cases per group.

n1=n2=2×(Zα2+Zβ)2×σ2(μ2−μ1)2

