## Methods

### Design

The study is a randomized controlled trial (RCT). A total of 174 post-acute ankle sprain patients will be recruited and randomly divided into the intervention group and the control group at a ratio of 1:1. Recruitment of eligible patients will begin from January 2025. Participants of the intervention group will be treated with TCAWM and participants of the control group will be treated with routine treatment. The whole study period will be 2-week including baseline and 2-week treatment. The study design is illustrated in the flow chart in Fig 1. The study protocol was approved by the Regional Ethics Review Committee of Shuguang Hospital (number: 2024-1535-118-01).

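### The 20% dropout allowance is slightly too small: 87 per group matches 72 × 1.2, whereas keeping 72 after 20% loss takes 72/0.8 = 90; power at the planned dropout is about 78.6%, not 80%

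*Protocol article*

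**What the plan says.** The Sample size section of the protocol article compares two means on the VAS after two weeks. The experimental arm has "means μ_2_ = 0.04 after two weeks interventions" and the control arm has "means μ_1_ = 0.25, the standard deviation σ = 0.45". The error rates are given as "According to the formula, α = 0.05, β = 0.2", and the printed formula uses the α/2 quantile, so the test is two-sided. The section concludes that "the sample size of each group is calculated to be n = 72" and then makes the dropout allowance: "consider a 20% dropout rate, and the final sample size is 87 cases per group".

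The total carries through to the Design section ("A total of 174 post-acute ankle sprain patients will be recruited") and to the Methods paragraph of the Abstract, which also gives 174. Since 2 × 87 = 174, the enrolled numbers are consistent across the article.

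**The concern.** A dropout allowance is meant to leave the calculated number of evaluable patients after the expected losses. Here 72 per group is the number tied to β = 0.2, and 20% is the expected loss. Enrolling 87 does not leave 72 once 20% have gone. The required number, the dropout rate and the enrolled number all stand in the same section, and they cannot all hold together.

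What is at stake is the accuracy of the power statement, which the final report is likely to repeat. The Limitation section itself expects that unblinded control patients may be more likely to drop out, so a reader has reason to look at this margin.

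**Working it through.** **Inputs, all from the Sample size section:** means 0.04 and 0.25, so δ = 0.21; σ = 0.45; α = 0.05 two-sided; β = 0.2; dropout 20%; 72 per group before dropout and 87 after.

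**1. Reproduce the plan's 72.**
n = 2 × (z for α/2 + z for β)² × σ² / δ²
= 2 × (1.96 + 0.84)² × 0.45² / 0.21²
= 2 × 7.84 × 0.2025 / 0.0441 = 72.0.
With unrounded quantiles the result is 72.08, which strictly rounds up to 73. The stated 72 is accepted here.

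**2. Reproduce the plan's 87.**
- Adding 20% to the evaluable number: 72 × 1.2 = 86.4, rounded up to 87. This matches.
- Dividing by the fraction retained: 72 / (1 − 0.20) = 90. This does not match.

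**3. What 87 leaves at the planned dropout.**
87 × 0.80 = 69.6 per group, against 72 required. To keep 72, a group can lose at most 87 − 72 = 15 patients, and 15/87 = 17.2%.

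**4. Power at that number.**
Normal formula: power = Φ(δ / (σ√(2/n)) − 1.96).
- n = 72: 0.21 / (0.45 × √(2/72)) = 2.800; 2.800 − 1.960 = 0.840; power 80.0%.
- n = 69.6: 0.21 / (0.45 × √(2/69.6)) = 2.753; 2.753 − 1.960 = 0.793; power 78.6%.
- In whole patients: 78.3% at 69 and 78.8% at 70.

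The noncentral t distribution gives 79.4% at 72 and 78.0% at 69.6.

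| Completers per group | Normal formula | t method |
|---|---|---|
| 72 (required) | 80.0% | 79.4% |
| 69.6 (87 less 20%) | 78.6% | 78.0% |

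Within either method the loss is about 1.4 points. The gap in enrolment is 90 − 87 = 3 per group, or 180 − 174 = 6 in total.

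**The case against.** The case for leaving this alone has several parts.

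- *The inflation step is not printed.* This is true: 72 × 1.2 is inferred because it gives exactly 87, and the article attaches β = 0.2 to 72, not explicitly to 87 less 20%. The point does not depend on how 87 was reached, because 87 × 0.8 falls below 72 by any route.
- *The gap is smaller than the uncertainty in the inputs.* If the means and SD are values rounded to two decimals (an assumption), δ could lie between 0.20 and 0.22 and σ between 0.445 and 0.455. The same formula then gives roughly 64 to 81 per group. The Limitation section also concedes that preliminary data were insufficient and calls the study preliminary and exploratory. This limits the importance of the error but does not make the stated figures agree.
- *Actual loss may be lower, and the analysis is by intention to treat with multiple imputation.* The treatment period is short, partly to limit dropout, and 87 tolerates 17.2% loss. But the section itself chose 20%, and imputation does not in general restore the information lost with missing outcomes.

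In the other direction, a reader might infer that the trial is materially underpowered, or that recruitment has to rise to 180. The documents do not support either reading: on the plan's own inputs the loss is about 1.4 points. Nor would 90 per group secure a strict 80%. By the t method 72 completers already give only 79.4%, and starting from 73 the enrolment would be 73/0.8 = 91.25, so 92 per group.

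**Conclusion.** The error is real and minor. The stated 87 per group does not keep the required 72 evaluable patients at the stated 20% dropout. About 70 remain, and power is about 78.6% instead of 80.0% by the plan's own formula.

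This takes the plan's δ and σ as given, assumes exactly 20% loss in each group, and counts only patients with an observed outcome as contributing to power. Nothing elsewhere in the article repairs the inconsistency, and nothing in the design or analysis has to change because of it.

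**What to change.** Keep 174 patients and replace the dropout sentence in the Sample size section with one that is true of 87 per group. For example: *87 per group leaves 72 evaluable with up to about 17% dropout; at 20% dropout about 70 per group remain and power is about 79%.* The Design section and the Abstract can stay as they are.

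The cost is one sentence and a slightly less favourable stated power, with no new patients. If the sponsor prefers to keep the 20% allowance with 72 evaluable, the matching figure is 90 per group (180 in total), which is six more patients. The size of the shortfall does not require this.

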### Randomization and allocation concealment

The patients who meet the diagnosis of post-acute ankle sprain and sign informed consent will be randomly assigned to control group and intervention group at a ratio of 1:1. Randomization will be computer generated by independent and uninformed statistical experts. Managers who do not participate in the recruitment and treatment place each number in an opaque envelope and keep it. After screening the patients, the doctor responsible for recruitment will contact the administrator who will send the file to the eligible participants and inform them of the allocation.

### Blinding

Due to the nature of the intervention, therapists and participants cannot be blinded. So we provide standard training to patients before they receive intervention, including informing them of the intervention methods and specific implementation, as well as self-assessment methods (VAS、SF-MPQ) for the efficacy after intervention; We have not only established self-assessment during the evaluation process, but also established third-party objective evaluations, and the third-party evaluators will also receive standard training including standardized use of equipment for evaluation to reduce the impact of intervention expectations. During the study, statisticians, administrator, data collectors and result evaluator will be blinded. After the statistics, the blinding method will be broken.

### Data collection and management

Two data administrators who do not belong to the research team and blinded to group allocation will be responsible for data entry and database establishment. We will implement a systematic approach to monitor participant retention throughout the study. This will include regular assessments of participant engagement and reasons for dropout, which will be documented and reported in our final analysis.Meanwhile,We will transparently report the extent and nature of missing data in our study. This will include the percentage of missing data for each variable, the reasons for missingness, and the methods used for imputation. This transparency will allow readers to assess the potential impact of missing data on our conclusions.To minimize dropouts, we will implement strategies aimed at enhancing participant engagement, such as regular follow-ups, reminders, and providing incentives for continued participation. All original data related to the study will be stored at Shuguang Hospital Affiliated to Shanghai University of Traditional Chinese Medicine and uploaded in real time to the China Clinical Trial Registry.

### Statistical analysis

For all outcomes, we will perform intent to treat analysis for our primary assessment of efficacy and a supplementary per protocol analysis. Use SPSS 21.0 statistical software for statistical analysis, including descriptive statistics such as mean, standard deviation. Quantitative data are analyzed using methods such as analysis of variance. Count data is analyzed using chi square test, Fisher’s exact test; Non parametric rank sum test and CMH chi square test is used for rank data. Set α = 0.05 as the significance test level, and when P<0.05, it indicates that the difference is statistically significant.

We will perform the following subgroup analyses: sex, men versus women; age, comparing outcomes for participants aged ≤30 versus >30; injury characteristic, non-sports versus sports injury; and grade 1 versus grade 2 sprain. To estimate significance of the subgroup treatment effect modification we use a Wald test of the treatment by subgroup interaction term from a logistic regression model.

To evaluate effects of missing data,we will employ appropriate data imputation methods to minimize bias. Specifically, we plan to use multiple imputation techniques, which allow us to create several complete datasets by filling in missing values based on observed data patterns. This approach will help us to better estimate the parameters of interest while accounting for the uncertainty associated with missing data.

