**Methods:**

This study is a single center, prospective, intervention randomized controlled trial with a control group. 174 patients of 18–35 years old with post-acute ankle sprain will be included. A randomized controlled study is conducted and divided into a control group and an experimental group. The control group receive routine treatment, while the experimental group receive integrated traditional Chinese and western medicine rehabilitation programs. The intervention lasted for a total of 2 weeks. The main outcome measures are Visual Analog Scale and Short Form McGill Pain Questionnaire; the secondary outcome measures are the Foot Ankle Ability Assessment Scale, AOFAS Ankle Posterior Foot Scale, torque and gait. This study protocol aims to evaluate the safety and effectiveness of integrated traditional Chinese and western medicine rehabilitation programs by comparing the results of two groups before and after treatment. This protocol will follow the SPIRIT guidance.

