## Introduction

Ankle sprain is one of the most common injuries during our clinic career. Ankle sprain often occurs with foot inversion or adduction, and most often happens at the lateral ankle [1]. The risk factors for ankle sprains include limited range of motion of the ankle joint, poor coordination function, weakened balance function [2,3], decreased proprioception and insufficient muscle strength [4–6], and even decreased cardiovascular and pulmonary function [4,7]. Exercise is the highest risk factor for ankle sprain occurrence [8]. About 40% of patients develop into chronic ankle sprains with persistent symptoms [9,10]. Usually, we consider the acute period refers to the first 1–2 weeks after injury. And, the term “post-acute” replace "subacute" to characterize the time after the acute period to the 12-month point. Literature has found that 60% of individuals achieve resolution of activity limitations and participation restrictions by the 12-month point [11]. And often we tend to refer to chronic ankle sprain as ankle instability which prolongs patient pain, affects patient’s life, enlarges treatment costs and social burden [12]. Thereby, we consider the post-acute period as an important phase for ankle sprain recovery.

Due to the fact that the ankle joint is an important load-bearing bone joint, its stability and function are crucial for daily activities and exercise. Although there are currently multiple treatment methods for ankle sprains, there are differences in the efficacy and safety of different methods [7,13]. The study of effective treatment methods for post-acute ankle sprains has important clinical significance.

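### The only method named for quantitative outcomes makes no use of the week-0 scores; a baseline-adjusted model should be named, with a gain for VAS that may be small

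*Protocol article*

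**What the plan says.** In the Protocol article, Statistical analysis, the sentence on continuous outcomes is "Quantitative data are analyzed using methods such as analysis of variance". No other method is named for VAS, SF-MPQ, FAAM, AOFAS, torque or gait, and no section mentions a covariate or an adjusted model. The same section promises an intention-to-treat primary assessment, multiple imputation, and a subgroup analysis by sprain grade.

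The Abstract (Methods) says the programme will be evaluated "by comparing the results of two groups before and after treatment", without saying how the earlier measurement enters the comparison. Sample size treats the trial as an unadjusted comparison of two post-treatment VAS means, with "α = 0.05, β = 0.2".

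Baseline scores will exist. Design states "The whole study period will be 2-week including baseline and 2-week treatment", and Table 1 ticks all six outcomes at week 0, week 2 and 3 months. Table 1 also places randomisation and allocation at week -1, one column before the first outcome measurement.

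**The concern.** Entry is broad. The Inclusion criteria admit grades I and II and set no minimum VAS. The Introduction uses the term post-acute "to characterize the time after the acute period to the 12-month point", so time since injury can range from a couple of weeks to a year. Baseline pain and function can be expected to vary, and the Randomization section describes no stratification. Nothing described in the design or analysis therefore deals with a chance difference in baseline scores.

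Two things are at stake. The first is precision: variation in the week-2 score that baseline could explain stays in the error term. The second is the estimate in the trial actually run: if one arm happens to start with more pain, an unadjusted week-2 comparison carries part of that difference. The open wording also leaves a post-score, a change-score and a repeated-measures ANOVA all available, and these differ in power.

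**Working it through.** **Inputs from Sample size.** Control mean 0.25 and experimental mean 0.04 at two weeks, so the difference is 0.21; SD 0.45; alpha 0.05 two-sided (the formula uses Z at alpha/2); power 80%; dropout 20%; 87 per group. Rho is **not in the article** and is assumed over a range.

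**Step 1: the plan's own figure.** n = 2 × (1.96 + 0.84)² × 0.45² / 0.21² = 72.0 per group (72.08 with unrounded normal quantiles). The stated 72 reproduces, as an unadjusted comparison of post-treatment means.

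**Step 2: unadjusted power at the expected evaluable number.** 87 × 0.8 = 69.6 per group. Standardised effect = (0.21 / 0.45) × √(69.6 / 2) = 0.4667 × 5.899 = 2.753. Power = Φ(2.753 − 1.960) = Φ(0.793) = 78.6%.

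**Step 3: power with the baseline score as covariate.** The residual SD becomes 0.45 × √(1 − rho²), so the standardised effect is 2.753 / √(1 − rho²).

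| rho (assumed) | 1 − rho² | Standardised effect | Power at 69.6 per group |
|---|---|---|---|
| 0 | 1.00 | 2.753 | 78.6% |
| 0.1 | 0.99 | 2.767 | 79.0% |
| 0.2 | 0.96 | 2.810 | 80.2% |
| 0.3 | 0.91 | 2.886 | 82.3% |
| 0.4 | 0.84 | 3.004 | 85.2% |
| 0.5 | 0.75 | 3.179 | 88.9% |

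A rho of about 0.19 brings power to 80%.

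**Step 4: where rho may lie for VAS.** The planned week-2 means are 0.25 and 0.04 on a 0–10 line, with an SD (0.45) larger than either mean. Most week-2 scores would then be at or near zero, which limits how strongly they can follow baseline. The upper rows of the table are the cautious ones for VAS. The article plans no such floor for the other outcomes.

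**Step 5: chance imbalance.** With 69.6 per group, one standard error of the baseline difference is √(2 / 69.6) = 0.170 SD. Assuming equal SDs at baseline and week 2, an imbalance of that size shifts the unadjusted VAS difference by rho × 0.170 × 0.45:
- rho 0.1: 0.008, or 4% of 0.21
- rho 0.3: 0.023, or 11%
- rho 0.5: 0.038, or 18%

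**Step 6: if ANOVA means change scores or time by group.** The SD is then 0.45 × √(2(1 − rho)). At the planned 72 per group, power is 65.8% at rho 0.3 and 80.0% at rho 0.5, against 83.5% and 89.9% for ANCOVA. Adjustment does better on this reading too.

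**Step 7: order of events.** Table 1 has allocation at week -1 and VAS first at week 0. Randomization and allocation concealment says participants are told their group; Blinding says they cannot be blinded and rate VAS and SF-MPQ themselves. On this schedule the week-0 score is taken before treatment but after allocation, and possibly after the participant knows it.

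**The case against.** The strongest reply is that nothing here is an error. The wording gives ANOVA as an example and does not exclude a covariate. The document is a condensed article, and an unseen analysis plan may specify ANCOVA. The trial is sized for an unadjusted comparison, and a two-group ANOVA matches that. All of this stands, and it limits the point to an improvement. It does not remove it: ANOVA is the one method the article commits to, the sample size is unadjusted too, and the better use of data already collected is easy to state.

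A reader might infer more than the article supports:

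- **That the ANOVA is biased or invalid.** Under randomisation it is unbiased on average and keeps its type I error. ANCOVA, for its part, corrects only for the covariates entered.
- **That ANOVA results cannot be pooled over imputed datasets.** With two arms, ANOVA is the same linear model without covariates, and its mean difference and standard error pool just as directly.
- **That within-group tests are planned.** The Abstract's phrase, "comparing the results of two groups before and after treatment", describes a between-group comparison, and no within-group test appears anywhere.
- **That lack of adjustment causes the shortfall below 80%.** The 78.6% arises because 72 was multiplied by 1.2 (86.4, rounded up to 87), where dividing by 0.8 would give 90. That is a separate matter.
- **That a pre-randomisation baseline is already in hand.** On Table 1's schedule it is not.

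**Conclusion.** The point holds as a worthwhile, low-cost improvement. The article names an unadjusted method for outcomes whose baseline values it collects. The unadjusted analysis is valid but less precise, and it leaves chance baseline imbalance in the estimate.

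The size rests on an assumed rho and on the plan's own difference and SD. For VAS the gain at 69.6 per group runs from negligible (78.6% to 79.0% at rho 0.1) to about ten percentage points (88.9% at rho 0.5), and the planned floor makes the lower part of that range plausible. No large gain should be promised for VAS. Outcomes without such a floor may gain more, but the article gives no figures to show it. The week-0 score is a sound covariate only so far as knowledge of allocation has not influenced it.

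**What to change.** 1. State the primary analysis as a linear model (ANCOVA) of week-2 VAS on treatment and week-0 VAS, with sprain grade as a further covariate. Add time since injury if the medical history records it; Table 1 does not list it as an item.
2. Report the adjusted between-group mean difference with its 95% CI, pooled over the imputed intention-to-treat datasets.
3. Use the same form for SF-MPQ, FAAM, AOFAS, torque and gait, each with its own week-0 value.
4. Place the baseline assessment before allocation is disclosed. If that cannot be done, say in the report that the baseline covariate was measured after allocation but before treatment.

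Items 1 to 3 change wording only and need no extra patients or measurements, apart from confirming that time since injury is recorded. Item 4 is a change to the order of visits, or failing that one sentence in the report.
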